**- Proportion of eligible villages where drugs for sIPTc were delivered.**

Criterion used: presence in the village on 1st September, 1st October and 1st November of persons trained to give preventive treatment to children (all 725 villages investigated) and evidence of administration of drugs to at least 50 % of the children mentioned in the register in villages receiving sIPTc. Reasons for logistical problems will be followed up through interviews with those involved**.**

**- Proportion of eligible children who received one, two and three doses of sIPTc.**

Criteria used: (1) children who received one, two and three doses of sIPTc as indicated in the register; (2) presence of sulfadoxine-pyrimethamine in the capillary blood of a sample of 300 eligible children (sampling during the two first weeks of September, October and November; children will be selected using a cluster survey design with villages selected with probability proportional to size. The parents of children who did not receive the full three doses will be interviewed to find out the reasons for default. This part of the study will be done using similar methods to those developed for surveys of vaccination coverage.

**- equitability of access to the intervention in relation to health and wealth indicators**

To determine equitability of access to the intervention in terms of health, wealth, and access to other interventions, we will record ITN use, vaccination history, nutritional status, and household assets for determining wealth quintile during the cluster sample survey.

**- Modalities of community participation and interactions with the health system and the project staff*.***

The respective roles of the nurse in charge of each health post and of the project staff in charge of a given intervention zone and of the community, in the success or the failure of sIPTc in each given village will be evaluated. In-depth interviews will be held to obtain detailed information on the factors that contributed to either success or failure. In addition to the previous criteria, other quantitative or qualitative criteria will be used, including monthly number of consultations, monthly number of infants vaccinated and the proportion of the population covered by the health post, availability of essential drugs in the health post and approaches used to improve participation in sIPTc and its linkage with routine activities in general, and EPI in particular. For 10 villages with maximum participation in sIPTc and 10 villages with low or no participation in sIPTc, additional investigations will include focus group discussions and participant observation at the village level.

2. Measurement of the impact of the intervention

**- All cause mortality and malaria-specific mortality**

All deaths occurring in eligible children during the year will be investigated by the verbal autopsy method with the same questionnaire and procedures used since 1984 for the sites of Niakhar, Mlomp and Bandafassi in Sénégal (Trape *et al.* 1998). In each village we will identify reporters who will record any death of a recruited child in the study area in a register. Study staff will also visit each village on a monthly basis to check the registers. A verbal autopsy will be completed for each recorded death within one month following the death using a standardized questionnaire (Garenne and Fontaine, 1986 (unpublished)). Non-medical interviewers who are members of the community and speak the local language will make household visits. Two physicians will sequentially review each verbal autopsy questionnaire. Cause of death will be attributed and followed by an independent assignment of ICD-9 codes. If the two physicians disagree, a panel of physicians involved in the Senegalese Working Group will discuss the case and reach a consensus diagnosis. If no consensus can be reached the cause will be recorded as unknown.

**- Incidence of hospital cases of severe malaria**

The area is served by two small district hospitals (Bambey and Mbour). There are referral hospitals at Thies and Fatick. Hospital admissions with severe malaria (i.e. malaria that presents with life threatening conditions, including coma, severe anaemia, renal failure, respiratory distress syndrome, hypoglycaemia, shock, spontaneous haemorrhage, and convulsions) will be documented. Records will be kept of admission of study children. Physicians and nurses based at these facilities will check whether children with severe malaria live in the study area, and record carefully details from their malaria ID card, and clinical biochemical and parasitological data will be recorded on a Case Report Form, with treatment details, final diagnosis using standard WHO criteria, and outcome.

**- Prevalence of anemia and parasitemia**

Hemoglobin measurements using a *Hemocue* machine, and finger prick sampling for thick smears for parasite density determination, will be done once in each stratum, at the end of transmission season, in a sub-sample of children. For these endpoints, 150 children will be randomly selected from each cluster. A slide will be declared negative only after 200 high power fields are examined without finding a parasite. A second independent laboratory technician will reread all collected slides. If parasite densities recorded by the two readers differ by more than 30%, a third senior laboratory technician will be asked to adjudicate. Anemia will be defined by hemoglobin level of less than 8 g/dL.

**- Prevalence of clinical malaria**

Impact on clinical malaria will be determined through limited passive surveillance, used to estimate the proportion of fever cases that have malaria, and by determining the prevalence of clinical malaria, defined as fever with asexual parasitaemia above a cut-off of 3000/ul, in the cross-sectional surveys in December.

**- Nutritional status**

Nutritional status will be measured each year at the end of the transmission season, in a random sample of 150 children per cluster. Weight for age index will be used as an estimate of the prevalence of malnourished children.

**- Drug sensitivity of *P. falciparum***

In order to assess the impact of the intervention on the sensitivity of *P. falciparum* to antimalarials, *in vivo* tests and molecular markers studies will be undertaken.

For sulfadoxine-pyrimethamine resistance investigations, molecular markers studies (DHFR and DHPS) will be conducted each year at the community levels, before and after the intervention. In addition to the thick smear, a drop of blood will be taken on a filter paper in a random sample of children at the end of the malaria season transmission., Markers of resistance to pyrimethamine and sulfonamides will be detected using a PCR assay as previously described (Pearce et al. 2003)

For evaluation of sIPTc for all these endpoints, data from Stratum A in year 1, Stratum B in year 2 and Stratum C in year 3 will be used in a stratified analysis comparing zones with and without sIPTc (Figure 4).

3. Safety studies

**- Toxicity**

Both sulfadoxine-pyrimethamine, amodiaquine and artemisinin derivatives have low toxicity and are widely used in malaria endemic countries for the curative, presumptive and/or preventive treatment of malaria among infants, children, pregnant women and adults. Artemisinin based combination therapy is recommended by WHO for treatment of malaria. SP plus. amodiaquine has until recently been the first line antimalarial in Senegal (now changed to AQ/AS) and has been widely used in this population.

In each health post, the nurse will hold a register where all cases of side effects possibly attributable to the trial drug treatment will be noted. Nurses will be taught to look out for severe skin lesions that might be associated with SP administration. A physician will investigate any reports. If severe side effects are suspected, a specific form will be filled and immediately transmitted to the Data and Safety Monitoring Board (DSMB). In October and December each year, the Principal Investigator (Intervention) of the project will transmit to the DSMB a synthesis of data collected by the nurse on the possible mild side effects attributable to sIPTc.

Figure 4: Stratified analysis in Stratum A in year 1, Stratum B in year 2 and Stratum C in year 3

**Stratum A** **Stratum B** **Stratum C**

|  |  |  |  |  |  |  |  |  |  |  |  |  |  |  |  |  |  |  |  |  |  |  |
| --- | --- | --- | --- | --- | --- | --- | --- | --- | --- | --- | --- | --- | --- | --- | --- | --- | --- | --- | --- | --- | --- | --- |
| Year 1 |  |  |  |  |  |  |  |  |  |  |  |  |  |  |  |  |  |  |  |  |  |  |
|  |  |  |  |  |  |  |  |  |  |  |  |  |  |  |  |  |  |  |  |  |  |  |
|  |  |  |  |  |  |  |  |  |  |  |  |  |  |  |  |  |  |  |  |  |  |  |
| Year 2 |  |  |  |  |  |  |  |  |  |  |  |  |  |  |  |  |  |  |  |  |  |  |
|  |  |  |  |  |  |  |  |  |  |  |  |  |  |  |  |  |  |  |  |  |  |  |
|  |  |  |  |  |  |  |  |  |  |  |  |  |  |  |  |  |  |  |  |  |  |  |
| Year 3 |  |  |  |  |  |  |  |  |  |  |  |  |  |  |  |  |  |  |  |  |  |  |
|  |  |  |  |  |  |  |  |  |  |  |  |  |  |  |  |  |  |  |  |  |  |  |
|  |  |  |  |  |  |  |  |  |  |  |  |  |  |  |  |  |  |  |  |  |  |  |
| Year 4 |  |  |  |  |  |  |  |  |  |  |  |  |  |  |  |  |  |  |  |  |  |  |
|  |  |  |  |  |  |  |  |  |  |  |  |  |  |  |  |  |  |  |  |  |  |  |
|  |  |  |  |  |  |  |  |  |  |  |  |  |  |  |  |  |  |  |  |  |  |  |
|  |  | = 2 zones (4000 children) where sIPTc is implemented | | | | | | | | | | | | | | | | | | | | |
|  |  |  |  |  |  |  |  |  |  |  |  |  |  |  |  |  |  |  |  |  |  |  |
|  |  | = 2 zones (4000 children) where sIPTc non yet implemented | | | | | | | | | | | | | | | | | | | | |
|  |  |  |  |  |  |  |  |  |  |  |  |  |  |  |  |  |  |  |  |  |  |  |

**- Rebound effect**

It will be important to compare malaria incidence after the age of 5 in children who received IPT with those that did not receive IPT, in order to determine whether sIPTc impairs acquisition of natural protective immunity. This will be done through a case control approach, cases will of two types, all deaths in children in the study area, and all hospital cases of severe malaria, among children over 5yrs, but young enough to have been eligible for IPT. For each case, controls will be sought, for cases and controls IPT doses received will be determined from the malaria card and cross checked against the study database, and the risk of death or severe disease related to the duration of IPT treatment prior to age 5. Cases and controls will be recruited in years 2-4 in stratum A, years 3-4 in stratum B, and year 4 in stratum C.

4. Costs effectiveness studies

The methodology will follow an incremental cost-effectiveness approach with the drugs being delivered through communities in the intervention zones. Cost-effectiveness Ratios (CERs) will be estimated for each condition in terms of cost per death and cost per hospital case of severe malaria averted.

A broader societal perspective will be taken with emphasis not only on the costs to the providers but also both direct and indirect costs for patients, their caregivers and the community.

Tools for data collection

A set of standard instruments will be used, similar to those used in other IPT studies. So far the following tools have been earmarked for adaptation and use in the Senegalese study:

- A data sheet for recording IPTi/sIPTc delivery costs at the district level.

- A data sheet for recording management and joint costs of the health system, reflecting both trial protocol and real program conditions.

- A set of data sheets for recording (expected) health system savings due to less malaria morbidity, based on the number of clinical cases avoided, health seeking patterns, and health service unit costs.

- A questionnaire for recording patient costs, through interviews.

Sample size requirements

In accordance with the guidelines of the CEWG, the sample size will be determined based on an ability to show an economic difference where one exists, to 95% of confidence. Sample sizes will be calculated for:

- Health system savings – i.e. a sample of the number of health facilities providing health care to study patients.

- Patient costs and savings – i.e. a sample of the infants receiving sIPTc and benefiting from less illness.

Proposed economic and Health outcomes

Table 1 shows the expected data to be collected, covering both cost and health outcomes. The study will collect costs on the delivery of sIPTc at the operational level, as well as cost offsets and patient costs (CEWG, 2004). Since the study is also interested in a real policy change and all the processes that go with a policy change, these costs will also be measured and presented. Inclusion of these costs is also important in a cost-effectiveness analysis, especially where such costs are significant and persist over time (CEWG, 2004).

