### SENEGAL

Guinea Bissau

Guinea Republic

TRIAL DESIGN

1. Study population

The study population will number approximately 450,000, including 95,000 children under the age of five years (2002 national census). The study area will be divided into 48 intervention zones, each one corresponding to one health post and its related villages. On average, 15 villages and 1975 children under five years of age will be the responsibility of each health post. The chief of the village, or a person designated by him, will establish a register of eligible children. This will be done under the supervision of the nurse in charge of the health post. This register will remain permanently in the village and a copy will be kept in the health post. Community consent will be obtained for the sIPTc intervention; individual consent will be sought from parents or guardians from a subgroup for participation of children in cross-sectional surveys.

Recent surveys conducted by NetMark show that coverage of Insecticide Treated Nets (ITNs) has increased in the study area and this is expected to increase with the widespread provision of ITNs at highly subsidized cost.

2. Design, sample size and power calculations

Due to logistic constraints and the need for staff training and community sensitization, it is not feasible to introduce the intervention in all zones simultaneously and it must be phased in gradually. This provides the opportunity for evaluation by comparing intervention areas with areas that have not yet received the intervention. The order of implementation will be randomized to permit unbiased comparison of mortality rates. To enable the most efficient evaluation, zones will be grouped into strata of zones such that mortality rates are as similar as possible in the zones within each stratum, using the best proxies available for the under 5 mortality rate. We plan phased introduction over 3 years, so there are three strata, the order of implementation of sIPTc in each stratum will be determined by randomization (Figure 2). The definition of the strata, and the order in which strata receive the intervention, will be decided in close consultation with the Ministry of Health. The project statistician will determine the order of implementation within strata.

Figure 2: Phased introduction of the implementation in the population divided onto 3 strata

Stratum A B C

Year 1 X0

Year 2 XX X0

Year 3 XX XX X0

Year 4 XX XX XX

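### For deaths and hospital severe malaria, the only stated rebound analysis compares children by the IPT doses they took; add a contrast by the seasons their zone was allocated.

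*Combined protocol and SAP*

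**What the plan says.** The protocol lists the risk of rebound after IPT stops among its specific objectives. Under Safety studies, Rebound effect, the aim is to "compare malaria incidence after the age of 5 in children who received IPT with those that did not receive IPT". There are two case types, both in children over five who were young enough to have been eligible: deaths, and hospital cases of severe malaria. On controls the text says only "For each case, controls will be sought". Exposure is individual: "for cases and controls IPT doses received will be determined from the malaria card and cross checked against the study database". The analysis is to have "the risk of death or severe disease related to the duration of IPT treatment prior to age 5". Recruitment windows are given by stratum ("Cases and controls will be recruited in years 2-4 in stratum A, years 3-4 in stratum B, and year 4 in stratum C"). No matching factors, covariates, model, sample size or power are stated.

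The design section (Design, sample size and power calculations) says "the order of implementation of sIPTc in each stratum will be determined by randomization", with the purpose that "The order of implementation will be randomized to permit unbiased comparison of mortality rates". Under Phased introduction, 8 of the 16 zones in Stratum A start in year 1, chosen at random, and the other 8 start a year later.

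The SAP has its own rebound analysis, within its Malaria incidence section. It compares incidence in the year after intervention between PSP areas (the SAP's label for intervention areas) and control areas. The age bands stand for how many earlier years of IPTc children had, and the model is an age-adjusted Poisson regression with a random effect. Exposure there is by area, not by individual uptake.

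**The concern.** Village workers deliver the doses, so a child's dose count depends partly on the family. The plan expects this. Its sample-size section allows for incomplete coverage of the three doses. Its process measures include interviews with parents of children who defaulted, and a study "To determine equitability of access to the intervention in terms of health, wealth, and access to other interventions". Wealth, net use, vaccination and general care-seeking plausibly also affect later death and severe malaria, so a comparison by doses received mixes any loss of immunity with differences between families.

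The two case types differ in direction. For deaths, families who take more doses probably have lower underlying risk, which pulls the estimate down and can hide a rebound. For hospital cases, the same families may also reach hospital more readily, which would push the estimate up. The net direction there is unknown.

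Rebound is a safety question, and false reassurance is the costly error. Randomised start order offers a contrast free of this self-selection, and the case-control plan does not use it.

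**Working it through.** The documents give no effect size, power or sample size for the rebound study, so there is no plan figure to reproduce. The calculations below are illustrations from assumed inputs. Outcomes are treated as rare, so odds ratios approximate rate ratios.

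**1. What randomisation supplies.** Under the protocol's under-five rule, children of the same age and stratum differ by one offered season between early and delayed zones: 1 v 0 if they turned five before the delayed zones started, otherwise 2 v 1 or 3 v 2.

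**2. Seasons received v seasons allocated (2 v 1).** Assumptions: early and delayed zones 1:1; 70% of families take every season offered and 30% take none; takers' underlying risk is h = 0.8 or 0.7 of non-takers'; true rebound 1.15 per season.

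| Group | Share | Risk | h = 0.8 | h = 0.7 |
|---|---|---|---|---|
| Non-takers | 0.30 | 1 | 1.000 | 1.000 |
| Takers, delayed zones (1 season) | 0.35 | h × 1.15 | 0.920 | 0.805 |
| Takers, early zones (2 seasons) | 0.35 | h × 1.15² | 1.058 | 0.926 |

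Rate ratio per season received (log-linear Poisson slope across the three groups, solved numerically): 1.033 for h = 0.8 and 0.964 for h = 0.7.

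Allocated contrast = (0.3 + 0.7h × 1.15²)/(0.3 + 0.7h × 1.15):
- h = 0.8: 1.0406/0.944 = 1.102
- h = 0.7: 0.948/0.8635 = 1.098

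With no rebound, the slope on seasons received is 0.893 or 0.832, which looks protective. The allocated contrast is exactly 1.00.

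**3. A second model, ever v never.** R is the true rebound in takers, c the share taking doses in early zones while delayed zones are still untreated, and r takers' underlying relative risk.
- Within-zone ratio by receipt = rR
- Pooled ratio by receipt = rR ÷ {[2(1−c) + cr]/(2−c)}
- Allocated ratio = (crR + 1−c)/(cr + 1−c)

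For R = 1.2, c = 0.7, r = 0.7:
- within zone: 0.7 × 1.2 = 0.84
- pooled: 0.84 ÷ (1.09/1.3) = 1.00
- allocated: 0.888/0.79 = 1.12

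A true 1.2 is fully hidden within zones once r is 0.83 or less. Pooled over zones, it is hidden at r of 0.77, 0.70 and 0.48 or less, for c = 0.5, 0.7 and 0.9. Over c = 0.5-0.9 and r = 0.5-1.0 with no rebound, the pooled ratio runs from 0.60 to 1.00 and the allocated ratio stays at 1.00.

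**4. Precision of the allocated contrast.** Take the k of 0.25-0.30 from the sample-size section, assume it applies to over-fives, and use 24 v 24 zones (half of the protocol's 48). Between-zone variation alone gives SE(log ratio) = k√(2/24) = 0.072 to 0.087. With ln 1.10 = 0.095, z is 1.32 to 1.10, so two-sided 5% power is about 26% to 20% even with unlimited cases. An estimate of exactly 1.00 would still have an upper 95% limit of exp(1.96 × SE), about 1.15 to 1.19.

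**The case against.** A reader might infer that the plan as a whole ignores randomised roll-out when it looks for rebound. The documents do not support that. The SAP's comparison by area and age band is close to an allocation-based exposure and largely meets the concern for malaria incidence. What it leaves open is narrower: it names no rebound analysis of deaths, is silent on hospital severe malaria, and does not mention the case-control study.

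A reader might also infer that the bias must run towards reassurance. That is plausible for deaths, but not established for hospital admissions.

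The illustration can be challenged too. No uptake figure is given in the documents; the 70% in the sample-size section is efficacy, not coverage. In the model of step 2, a comparison among recipients only is unbiased (1.058/0.920 = 1.15), and the distortion enters when never-takers are put on the same slope without adjustment. Doses received also partly reflect randomised zone order, which weakens the bias when zones are pooled and uptake is high. And silence about the model does not commit the sponsor to a crude analysis. All of this stands, and it limits what can be said about size. It does not remove the problem that nothing in the text guards against self-selection. Controls drawn from the case's own zone, which the text does not exclude, would discard most of the randomised variation.

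The strongest objection is precision. A one-season contrast at about 20-26% power for 1.10 cannot settle the question, and it does not address cumulative duration. That is a reason to report the interval and to keep the duration analysis as secondary.

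Finally, the tidy one-season difference depends on the under-five rule. The SAP treats 60-119 months as an intervention age group, and its survey section has eligibility extending past 59 months in 2009 and 2010. Allocated seasons therefore have to be counted under the rule in force each year.

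**Conclusion.** The point holds for deaths and hospital severe malaria, and only for those. Their one stated rebound analysis uses self-selected exposure with no stated control source, matching or adjustment. Under the assumed inputs, a true rebound of 1.15 per season reads as 1.03 to 0.96 by seasons received and about 1.10 by allocation. With no rebound, the readings are 0.89 to 0.83 and 1.00. These sizes rest on assumed uptake, assumed lower risk in takers, and a pooled unadjusted slope, so they show that masking is possible at moderate selection, not that it will occur. The direction is probable for deaths and uncertain for hospital cases. Because the SAP already accepts area-based exposure for incidence, extending it to these two outcomes is an inexpensive improvement on a stated safety objective.

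**What to change.** In the protocol's Rebound effect section and in the SAP, for deaths and hospital severe malaria:

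- Define the main exposure as the number of seasons in which the child's health-post zone was allocated sIPTc while the child was of eligible age, from date of birth, the roll-out schedule and the eligibility rule in force that year.
- Compare children of the same age, stratum and calendar year. Do not restrict controls to the case's own zone. Treat the health-post zone as the cluster.
- Report this with its confidence interval as the main rebound contrast, and state that a null result is not evidence of no rebound.
- Keep doses received as a secondary dose-duration analysis, with control source and matching stated, adjusted for wealth, net use and vaccination where recorded.
- Say whether the case-control study is retained alongside the SAP's incidence comparison.
- Reconcile the protocol's definition of rebound as occurring after age five with the SAP's use of 60-119 months as an intervention age group, and state when a child's rebound period begins.

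The cost is mainly wording: the main exposure needs only zone, date of birth and roll-out dates. The adjusted secondary analysis may need more, because the protocol's equitability measure records wealth, net use and vaccination in a sample survey and not for every case and control. The statistical price is dilution (about 1.10 instead of 1.15 at the assumed 70% uptake) and the low precision shown above.
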